#### Outcome measures

Primary outcome measures are changes in the past-month gambling frequency and expenditure (i.e., money spent on gambling, irrespective of winnings) as assessed at baseline, post-intervention, and both follow-up sessions. The secondary outcome measures include changes in attentional (VPT) and approach (AAT) bias scores from baseline to the 3-month follow-up. Changes in depressive symptoms (BDI-II) and severity of gambling problems (SOGS) from baseline to the follow-up sessions are also explored, although not included as main outcomes. Intervention credibility and expectancies are also assessed with the Credibility/Expectancy Questionnaire [66] during the second session of training, to evaluate participants’ general experience with the study.

### Data analysis

Multiple imputation of missing data will be performed for intention-to-treat analyses. Before running all analyses, all variable distributions will be screened for normality assumptions and univariate outliers. The use of parametric or non-parametric statistical tests will be adjusted accordingly. Each training group will be compared to its control group to check for any baseline difference in demographics (e.g., age and gender), severity of gambling problems (SOGS), and alcohol use. When significant differences are found and the relevant baseline variables also correlate with the outcomes of interest, they will be added as covariates in subsequent analyses.

Changes in gambling frequency and expenditure from baseline to the 6-month follow up will be examined through two separate 2 (condition: active training vs. placebo) × 4 (time: baseline, post-intervention, 3-month and 6-month follow up) mixed analysis of variance (ANOVA) analyses, one per training module. Each CBM condition is contrasted against its control condition, with the baseline assessment as reference time point for the following time points.

Changes in gambling cognitive biases as a result of each CBM intervention will be explored with a 3 (time: baseline, post-intervention, 3-month follow up) × 2 (condition: active vs. placebo training) × 2 (stimulus category: gambling vs. control) mixed ANOVA for approach bias (i.e., AAT task) and a 3 (time: baseline, post-intervention, 3-month follow up) × 2 (condition: active vs. placebo training) × 2 (trial type: on top vs. after) mixed ANOVA for attentional bias (i.e., VPT task). Any change in depression symptoms and gambling problems would be explored using two 2 (condition: active vs. placebo training) × 4 (time: baseline, post-intervention, 3-month and 6-month follow-up) mixed ANOVA analyses, one per training module.

No multiplicity adjustment will be applied to correct for the multiple treatment arms since the two active training conditions are distinct treatments, compared to their own control condition. As mentioned earlier, in order to efficiently explore the main effects of both types of training modules, the design of the study involves running two clinical trials under the same protocol. Hence, the two trials can be considered as separate studies, making it unconventional to apply any adjustments to alpha levels. Furthermore, we emphasize that the study is strictly explorative in nature, so any significant findings should be received with some reservation until tested in further confirmatory RCTs, implying a lesser need for multiple-testing correction [67].

If significant effects of the CBM interventions on the cognitive bias and gambling outcomes are detected, a moderated mediation analysis for each CBM module will be carried out to explore the moderating effect of interference control capacity, impulsivity and baseline cognitive bias on the relation between CBM effects and the gambling outcome(s) [68]. Baseline cognitive biases, interference control capacity (Stroop task) and trait impulsivity (BIS-11) would be tested as moderators of the changes in cognitive bias resulting from training, which would further act as mediator of the change in the primary outcome(s).

Besides monitoring participant inclusion and drop-out, the analysis plan does not involve any interim analysis of collected data. The clinical trial will continue until the target sample size is reached unless participant attrition rate, defined as a drop-out at any moment after completing the baseline assessment, exceeds the expected 60% attrition rate of included participants [42]. The results of the study will be reported following the guidelines of the “Consolidated standards of reporting trials” (CONSORT) extension to non-pharmacological interventions [69].

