#### Randomisation

Upon completing the baseline assessment session, participants are automatically randomised by the computerised system into one of the four experimental conditions in two steps: first, participants are randomised into three main experimental arms (ABM, AppBM, or placebo) with a 1:1:1.25 allocation ratio. Participants assigned to the placebo condition are then further randomised to receive the placebo version of either the AppBM or the ABM training, with a final allocation ratio equal to 1:1:0.62:0.62. Both randomisation steps are stratified by gender (i.e., participants are randomly allocated to one of the conditions to which the fewest participants of their gender have been assigned so far). The two-step randomisation procedure and the uneven ratio over the four experimental conditions were designed to increase the chance of receiving at least one active training intervention, while still allowing for a univocal comparison of each active training module with their respective placebo condition. Allocation concealment is fully ensured, since participant randomisation is fully automated and performed by a computer algorithm.

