### Sample size

A conservative a priori power analysis (G*Power 3.1, open-source software [70]) required a sample size of 114 participants to detect a small-to-medium effect size (Cohen’s *f* = 0.15, equivalent to partial eta squared value of 0.02) for the interaction effect between time and experimental condition for each primary outcome, using mixed ANOVA. Power of 0.80, Bonferroni-adjusted type-I error probability of 0.025 (0.05/2 primary outcomes) and moderate correlation between the repeated measures of 0.3 were assumed. Based on a similar online CBM study for alcohol drinking problems [42], an additional 60% dropout rate at follow up was taken into account, leading to a final target sample size of 182 participants.

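### Covariates are to be picked by baseline significance tests, which almost never admits gender (the randomisation factor) and leaves the primary model to be chosen from the data

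*Protocol article*

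**What the plan says.** In the protocol article, Data analysis, the baseline step is set out per module: "Each training group will be compared to its control group" in order to "check for any baseline difference in demographics (e.g., age and gender), severity of gambling problems (SOGS), and alcohol use". The consequence of that step is fixed in the next sentence: "When significant differences are found and the relevant baseline variables also correlate with the outcomes of interest, they will be added as covariates". Both conditions must be met. No significance level is given for these tests, and the list of demographics is open-ended.

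Under Randomisation, "Both randomisation steps are stratified by gender", and the mechanism is described: "participants are randomly allocated to one of the conditions to which the fewest participants of their gender have been assigned so far". Gender is thus both the factor that allocation balances and a variable named for the baseline test.

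The primary analysis is a 2 (condition) by 4 (time) mixed ANOVA for each module. Baseline is one of the four time levels and the reference for the later ones. The article names no covariate in advance.

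**The concern.** In a properly randomised comparison, any baseline difference is due to chance. Testing it examines a hypothesis already known to be true, and the result says nothing about whether adjusting for the variable would improve the estimate. What matters is whether the variable predicts the outcome. The rule requires prognostic value and a significant imbalance together, so a strong predictor that happens to be balanced is discarded.

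Two further consequences follow from the text.

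- The factor that the randomisation deliberately balances is the one least likely to pass the test, so the analysis will normally ignore the design factor.
- The correlation condition uses outcome data. The covariate set is therefore known only after outcomes are seen, and it can differ across the four primary analyses (two outcomes in each of two modules).

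At stake are precision in a small trial, protection against a chance imbalance in a variable that predicts change, and a primary model fixed before the data are seen.

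**Working it through.** **Inputs.** Sample size: "leading to a final target sample size of 182 participants". Allocation: "with a final allocation ratio equal to 1:1:0.62:0.62". Assumed correlation between repeated measures: 0.3 (Sample size section). Alpha of the baseline tests: not stated; 0.05 two-sided assumed, 0.025 to 0.10 shown.

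**The plan's own figure.** The plan gives no number for the covariate rule, so only the sample size can be reproduced. The power analysis "required a sample size of 114 participants to detect a small-to-medium effect size". With partial eta squared 0.02, f = sqrt(0.02/0.98) = 0.1429. Two groups, four measurements, alpha 0.025, correlation 0.3 and power 0.80 then give 113, or 114 for two equal groups. The target follows as 114 × 1.6 = 182.4. The 182 is taken as given here.

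**Group sizes.** 182 / (1 + 1 + 0.62 + 0.62) = 56.2 per active arm and 0.62 × 56.2 = 34.8 per placebo arm, so about 56 versus 35 per module.

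**Smallest imbalance flagged.** The threshold is t(1 − alpha/2, 89) × sqrt(1/56 + 1/35), where the square root is 0.2155.

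| Alpha | Threshold (SD) |
|---|---|
| 0.10 | 0.36 |
| 0.05 | 0.43 |
| 0.025 | 0.49 |

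Realised imbalances of 0.2, 0.3 and 0.4 SD give p = 0.36, 0.17 and 0.07. At alpha 0.05 none of them would lead to adjustment.

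**Chance of a flag.** For age, South Oaks score and alcohol use, treated as three independent tests at 0.05: 1 − 0.95³ = 0.14. A flag still does not admit the variable, because the correlation condition must also be met.

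**Gender.** The two-step allocation was simulated as described, 2000 runs at each of four female shares (10, 20, 30 and 50%). The active-versus-placebo gender test was significant in 0 of 2000 runs at every share. The largest difference was about 3 percentage points. Simple randomisation gave about 4 to 5%. Restricting to completers after 60% random dropout gave about 1 to 2%.

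**Type I error.** This was simulated for a simple between-group comparison at 56 versus 35 with one candidate covariate (20,000 runs).

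| Covariate–outcome r | Stated rule | Pre-specified adjustment |
|---|---|---|
| 0.3 | 0.047 | 0.048 |
| 0.5 | 0.043 | 0.051 |

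The rule is slightly conservative, not liberal.

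**Imbalance and the primary test.** Let a covariate have correlation r with the outcome and an imbalance of d SD between groups.

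- If it acts equally at every visit, the contrast of a later visit with baseline is shifted by r×d − r×d = 0.
- If it is unrelated to the baseline outcome but related to later visits, the shift is the full r×d. For d = 0.42, just below the threshold, that is 0.5 × 0.42 = 0.21 SD or 0.3 × 0.42 = 0.13 SD. In a simple two-group comparison the corresponding conditional type I error is about 0.13 and 0.08. These are upper guides for assumed values of r.

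**Precision.** With outcome variance 1 at each visit and correlation ρ = 0.3, the variance at a single follow-up visit is 2(1 − ρ) = 1.40 for change from baseline and 1 − ρ² = 0.91 after adjustment for baseline. The ratio is 0.91/1.40 = 0.65. Adjusting for any other predictor with correlation r reduces residual variance by r² in a simple comparison: 9% at r = 0.3 and 25% at r = 0.5.

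**The case against.** The strongest reply is that the primary test is the time by condition interaction with baseline as a time level. Stable differences between people are already removed from both the estimate and its error term. A simulation of the planned ANOVA (56 versus 35, four visits, correlation 0.3, covariate correlated 0.5 with every visit) gave an interaction bias of 0.00 SD at an imbalance of 0.3 SD and 0.01 SD at 0.42 SD, with type I error 0.048 and 0.052. This stands, and it rules out several stronger readings that a reader might infer:

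- **That a 0.3 SD imbalance with r = 0.5 biases the result by 0.3 × 0.5 = 0.15 SD.** This describes a comparison of post-treatment values only, or a covariate that predicts change. The document gives no evidence that any listed covariate does so.
- **That omitting gender makes the error bars too wide whenever gender predicts gambling.** In the planned ANOVA, gender would have to predict change in gambling, on which the document gives no figure.
- **That there is a 19% chance of a flag (1 − 0.95⁴).** This counts gender as an ordinary 5% test, although the allocation rule makes a significant gender difference very unlikely. About 14% is the consistent figure for the other three.
- **That the selection step inflates false positives.** The simulations do not show it.

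It can also be said that the study calls itself exploratory and treats the two modules as separate trials, so different covariates across modules matter less. That lowers the stakes but does not justify the rule. The trial is still powered on these primary tests, and exploratory estimates also benefit from precision and a fixed model. Nor is this detail left to a fuller plan: the article states the selection rule outright.

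**Conclusion.** The concern holds in a limited form. The rule selects covariates on an uninformative criterion, in practice excludes the randomisation factor, and lets the data decide the primary model. At 56 versus 35 it ignores imbalances below about 0.43 SD, assuming the full 182 randomised and two-sided alpha 0.05; the range is 0.36 to 0.49 SD for alpha 0.10 to 0.025.

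The consequences are lost precision, conditional bias if an unflagged covariate predicts change, and a model not settled in advance. The documents do not support a claim of inflated average type I error, or of a fixed bias in the time by condition test. The comparison of 0.91 with 1.40 assumes equal variances and the protocol's correlation of 0.3 at a single visit. The ratio is (1 + ρ)/2, so the gain shrinks as the correlation rises, and it should not be read as the exact gain for the overall interaction test. This is a worthwhile improvement to the analysis, not a threat to the trial's validity.

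**What to change.** Delete the significance-based rule and report baseline characteristics descriptively, without tests. Pre-specify one model, identical for both modules and both primary outcomes:

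- Outcomes: the post-intervention, 3-month and 6-month values.
- Covariates: the baseline value of the outcome, gender and baseline South Oaks score, included whatever the observed balance.
- Baseline is no longer a level of time.

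If baseline is kept as a time level, it should not also be a covariate. Gender and South Oaks score should then enter with covariate by time terms, because a main effect alone leaves the interaction untouched.

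The cost is a small change to the model as well as to the wording. It takes a few degrees of freedom: one per covariate as a main effect, or three more for each covariate by time term over four visits. All the variables are already collected at baseline. Data collection was still under way when the article was written, and the outcome dataset is to be retrieved only at its end, so the change could be made before outcomes are seen.

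### The primary 2 × 4 ANOVA treats baseline as a fourth outcome level; it is valid, but at the plan's correlation of 0.3 a baseline-adjusted joint test is more efficient

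*Protocol article*

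**What the plan says.** The Data analysis section specifies, for frequency and expenditure, "2 (condition: active training vs. placebo) × 4 (time: baseline, post-intervention, 3-month and 6-month follow up) mixed analysis of variance (ANOVA) analyses", carried out separately for the two modules. Each active arm is set against its own placebo, "with the baseline assessment as reference time point for the following time points".

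The only route to a covariate is conditional: "When significant differences are found and the relevant baseline variables also correlate with the outcomes of interest, they will be added as covariates". The variables checked for imbalance are demographics, gambling severity and alcohol use. The baseline value of the primary outcome is not named.

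The Sample size section powers the trial "for the interaction effect between time and experimental condition for each primary outcome, using mixed ANOVA". It uses an effect size f of "0.15, equivalent to partial eta squared value of 0.02", a "Bonferroni-adjusted type-I error probability of 0.025 (0.05/2 primary outcomes") and says "moderate correlation between the repeated measures of 0.3 were assumed". On these inputs it "required a sample size of 114 participants" before allowance for dropout.

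The Randomisation section places allocation after the baseline session. The Baseline assessment section shows that past-month frequency and spending are recorded in that session.

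**The concern.** Baseline is measured before allocation, so the arms can differ on it only by chance. Entering it as an outcome level makes the condition × time interaction a comparison of changes from baseline. When the correlation between visits is below 0.5, subtracting a single baseline value adds more noise than it removes. The plan assumes 0.3 and then chooses a change-type contrast. The conditional covariate rule does not repair this, because it does not provide for routine adjustment for the baseline outcome.

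What is at stake is precision, not bias. Each module is tested only on its own active–placebo pair, so efficiency matters, and the data needed to recover it are collected anyway.

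**Working it through.** **Inputs.** From the Sample size section: correlation ρ = 0.3, alpha 0.025, partial eta squared 0.02, N = 114 before dropout, target 182, dropout 60%. From Data analysis: two groups, four time points. From Randomisation: final allocation 1:1:0.62:0.62. Assumptions added here: equal variance at each visit (set to 1), equal correlation between all visits, normality, complete data.

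**Reproducing 114.** Partial eta squared 0.02 gives f = √(0.02/0.98) = 0.143. For the within–between interaction, λ = f²·N·4/(1 − ρ) = 0.0204 × 114 × 4/0.7 = 13.29, with 3 and 3 × 112 = 336 df. Power is 0.807. N = 113 is the minimum, or 114 with equal groups. The stated figure is therefore the 3-df interaction with baseline as a level. (The printed f of 0.15 would give 102.)

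**Variances at ρ = 0.3.**
- One visit: change 2(1 − 0.3) = 1.40; follow-up value alone 1.00; baseline-adjusted 1 − 0.3² = 0.91. Ratio 0.91/1.40 = 0.65.
- Mean of three post-baseline visits: its own variance is (1 + 2 × 0.3)/3 = 0.533. Change: 0.533 + 1 − 0.6 = 0.933. Adjusted: 0.533 − 0.09 = 0.443. Ratio 0.475.
- The ratio for the mean is 0.417/0.667 = 0.625 at ρ = 0.5, and 0.310/0.400 = 0.775 at ρ = 0.7.

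**Noncentrality.** Let δ be the active–placebo differences at the three post-baseline visits and n_e = n₁n₂/(n₁ + n₂).
- Planned ANOVA: λ = n_e/(1 − ρ) × [Σδ² − (Σδ)²/4].
- Baseline-adjusted joint test: λ = n_e/(1 − ρ) × [Σδ² − ρ/(1 + 3ρ) × (Σδ)²].

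At ρ = 0.3, ρ/(1 + 3ρ) = 0.158, which is below 0.25. For any ρ below 1 it stays below 0.25, so the adjusted λ is never smaller, whatever the pattern of effect.

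**Power at f = 0.143, alpha 0.025, N = 114 (57 vs 57).** The effect per visit is scaled to the same f, so the planned ANOVA has λ = 13.29 throughout. The adjusted joint test uses N − 5 denominator df, and the averaged contrast N − 3.

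| Effect pattern (size in SD) | Planned ANOVA | Adjusted, joint 3 df (λ) | Adjusted, average only, 1 df |
|---|---|---|---|
| Sustained 1, 1, 1 (0.66) | 0.81 | 0.99 (27.99) | 0.999 |
| Fading 1, 0.5, 0 (0.69) | 0.81 | 0.90 (17.30) | 0.69 |
| One visit 1, 0, 0 (0.66) | 0.81 | 0.85 (14.93) | 0.31 |

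**Other sample sizes.** 182/3.24 = 56.2 per active arm and 0.62 × 56.2 = 34.8 per placebo arm, so 56 vs 35. With a sustained effect, power is 0.66 planned and 0.95 adjusted (joint). If only 40% supplied data, 22 vs 14: 0.25 and 0.50 for a sustained effect, but 0.246 and 0.249 for a one-visit effect.

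**The case against.** The best defence is coherence. The Outcome measures section defines the primary outcomes as changes, the interaction tests changes, and the sample size is built on that interaction and reproduces. The ANOVA is unbiased under randomisation, and the study calls itself strictly explorative. All this is correct, and it is why the point concerns efficiency rather than error. It does not favour the ANOVA, however. With baseline as covariate, the adjusted treatment difference is the same whether the response is the follow-up value or the change, so the question asked is retained.

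The gain also depends on ρ, which is a planning value, and it shrinks as ρ rises. This stands. At ρ = 0.5 with 22 vs 14 and a one-visit effect, the adjusted joint test is marginally worse (0.343 against 0.358), because it has fewer denominator df.

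Three stronger readings are tempting, and the documents do not support them:
- A reader might infer that the plan discards half its information. That holds only for an effect averaged over all three post-baseline visits. The plan names no such average, and for its visit-against-baseline comparisons the ratio is 0.65.
- A reader might infer that one averaged 1-df contrast is a free replacement. It is a different target, and it falls below the planned test for a fading or one-visit effect. The protocol nowhere assumes a constant effect.
- A reader might infer that this choice is what leaves the trial short of power. Any shortfall at 56 vs 35 or 22 vs 14 comes from splitting the sample into two pairs and from dropout, which are separate matters. The 22 vs 14 case is also not the planned analysis set, since multiple imputation is specified.

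**Conclusion.** The point holds as one of efficiency. The planned ANOVA is valid, but at the plan's own correlation it uses a contrast with variance 1.40 per visit where 0.91 is available (0.933 against 0.443 for the three-visit average). Adjusting for baseline while keeping a joint 3-df test has at least the ANOVA's noncentrality for every effect pattern. At N = 114 this takes power from 0.81 to between 0.85 and 0.99 over the three patterns tabulated. At 56 vs 35 with a sustained effect it takes power from 0.66 to about 0.95.

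These sizes rest on ρ = 0.3 between all visits, normality and complete data. In very small samples with an effect at one visit only, there is essentially no gain. The change is worth making, but nothing in the plan is invalidated if it is not made.

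**What to change.** For each module and each primary outcome, analyse the three post-baseline visits with a repeated-measures model containing the baseline value of that outcome as covariate (or a model constraining the arms to equal baseline means), visit, condition and condition × visit. Make the primary test the joint 3-df test of the condition effect across visits. Report the visit-specific and averaged differences with intervals. Enter the baseline outcome in every analysis, not subject to a test for imbalance.

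Make the averaged contrast primary only if the investigators state that a sustained effect is their target.

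The cost is some analysis wording and no extra participants or measurements. The Trial status section says data collection is ongoing, and the Blinding section says the outcome dataset is retrieved only at its end, so on those statements the change can be fixed and dated before outcomes are seen.

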### The present study: objectives and hypotheses

Being the first CBM study in the gambling field, the primary goals of the RCT are to explore (a) whether gambling behaviour decreases over time as a result of a CBM intervention, and (b) whether the two CBM interventions would successfully decrease or reverse the targeted bias. Primary outcomes are monthly frequency and expenditure (i.e., average amount of money spent per month) [46], assessed at baseline, after the intervention, and in the medium term (after 3 and 6 months). The secondary outcomes include measures of gambling-related attentional and approach bias, administered at baseline, after the intervention, and at the 3-month follow up. Participants’ severity of gambling problems and depressive symptoms are also monitored over all time points.

An additional secondary moderated mediation analysis will explore the moderating effects of trait impulsivity and interference control capacity (i.e., cognitive inhibition), which have been considered as endophenotypical vulnerability markers for SUD and GD [47, 48]. Greater impulsivity and diminished ability to cope with cognitive interference could lead to lesser ability to ignore gambling cues in the environment and to suppress prepotent behavioural responses, and could thus moderate the strength of the cognitive biases. In line with previous results of CBM studies in alcohol addiction [21, 35], any change in cognitive bias as a result of the training intervention would mediate changes in the gambling outcome variables. Further, participants with stronger cognitive biases and/or lower interference control capacity and higher impulsivity at baseline would benefit more from a CBM intervention than participants with weaker cognitive biases and/or stronger interference control capacity and lower impulsivity.

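### The only planned test of moderation and mediation is gated on significant average effects on both bias and gambling, which fits the moderator hypothesis badly

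*Protocol article*

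**What the plan says.** The section on objectives and hypotheses states the analysis without a condition: "An additional secondary moderated mediation analysis will explore the moderating effects of trait impulsivity and interference control capacity". It gives two directional hypotheses. The mediator hypothesis is that "any change in cognitive bias as a result of the training intervention would mediate changes in the gambling outcome variables". The moderator hypothesis is that "participants with stronger cognitive biases and/or lower interference control capacity and higher impulsivity at baseline would benefit more from a CBM intervention". The abstract also announces moderator and mediator analyses without a condition.

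The Data analysis section makes the analysis conditional. For each module it is to be run only "If significant effects of the CBM interventions on the cognitive bias and gambling outcomes are detected". Baseline bias, Stroop interference control and BIS-11 impulsivity are then the moderators, and change in bias is the mediator. No other test of moderation or mediation is described for the case where the condition fails. The same section calls the study strictly exploratory and, partly on that ground, applies no multiplicity correction across the arms.

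**The concern.** The gate asks whether training works on average. The moderator hypothesis asks whether it works better in some participants than in others. The second question can have a positive answer when the first does not: if benefit sits mainly in participants with strong bias or high impulsivity, the average over everyone is diluted and its test loses power. The rule is then most likely to block the analysis when the subgroup pattern is most marked.

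The rule also has a cost when it lets the analysis through. Interactions and indirect effects would be estimated only in samples where both the bias and the gambling differences were large enough to reach significance, so the estimates tend to be too large. That is unhelpful in a pilot whose purpose is to generate hypotheses for later trials.

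**Working it through.** **Inputs from the protocol.** Sample size section: Cohen's f = 0.15, described as "equivalent to partial eta squared value of 0.02"; "Power of 0.80, Bonferroni-adjusted type-I error probability of 0.025 (0.05/2 primary outcomes"); correlation ρ = 0.3; N = 114, raised to 182 for 60% dropout. Data analysis section: the gambling test is 2 conditions × 4 times per module, and the bias test has 3 times. Randomisation section: allocation 1:1:0.62:0.62.

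**Assumptions.** The protocol gives no effect size or alpha for the bias outcome. I take the same f, alpha 0.05, ρ = 0.3 and a condition × time test over 3 times.

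**Formula.** For the condition × time interaction with k = 2 groups and m times, λ = f²·N·m/(1−ρ), with df1 = m−1 and df2 = (N−2)(m−1). Power is the noncentral F probability beyond the critical value.

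**Reproducing the protocol's figure.** Partial eta squared 0.02 gives f = √(0.02/0.98) = 0.1429. With m = 4 and alpha 0.025, N = 113 gives λ = 13.18 and power 0.803. Rounded up to two equal groups this is 114, as stated. Taking f = 0.15 exactly gives N = 102, so the 114 rests on f = 0.1429, which I use below.

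**Participants per module.** 182/2 = 91, split about 56 active to 35 placebo. With 60% dropout, 91 × 0.4 = 36.4. For 1:0.62 allocation the equivalent equal-group size is n·4p(1−p) with p = 1/1.62, that is 0.945n: 86.0 and 34.4.

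**Power of each test.**

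| Participants per module | f | Gambling (m = 4, alpha 0.025) | Bias (m = 3, alpha 0.05) |
|---|---|---|---|
| 91 | 0.143 | 0.659 | 0.681 |
| 36.4 | 0.143 | 0.246 | 0.309 |
| 91 | 0.071 | 0.152 | 0.211 |
| 36.4 | 0.071 | 0.066 | 0.108 |

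The halved f in the last two rows represents half the participants having the planned effect and the rest none.

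**Probability that the gate opens.** If the two tests are independent it is the product of the powers. Whatever their dependence, it cannot exceed the smaller power. Positive dependence, which mediation would imply, lies between the two.

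| Participants per module | f | One gambling outcome: product to upper bound | Either outcome suffices: independent tests |
|---|---|---|---|
| 91 | 0.143 | 0.659 × 0.681 = 45%, to 66% | (1 − 0.341²) × 0.681 = 60% |
| 36.4 | 0.143 | 0.246 × 0.309 = 8%, to 25% | (1 − 0.754²) × 0.309 = 13% |
| 91 | 0.071 | 0.152 × 0.211 = 3%, to 15% | 6% |
| 36.4 | 0.071 | 0.066 × 0.108 = 1%, to 7% | 1% |

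Rounding 36.4 down to 36 moves the second row to 7% and 24%. If either outcome suffices, the upper bound at f = 0.143 is the bias power: 68% at 91 and 31% at 36.4. If both gambling outcomes must be significant, the independent figures fall to 30% and 2%.

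**The case against.** Several counter-arguments have force.

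- **Frequency.** A reader might infer that the hypotheses will usually go untested. The documents do not support that as a general statement. With near-complete information on 91 per module the gate opens about as often as not, or more often. The 36 per module is a floor, because the Data analysis section plans multiple imputation for intention-to-treat analyses. Imputation does not restore all the lost information, so the realistic value lies between the two rows. Low power at 36 is also a sample size matter, not a fault of the gating sentence.
- **Wording of the gate.** The condition names gambling outcomes in the plural, but the same sentence later uses a bracketed plural, which suggests that one may suffice. That raises the figures, as shown.
- **Mediation.** The mediator hypothesis itself presupposes a change in bias resulting from training, so asking for evidence of that change first is consistent with it. Requiring a significant total effect on gambling as well is debated practice, not a plain error. The case is therefore weaker for mediation than for moderation.
- **The gate limits output.** Three moderators, two gambling outcomes and two modules give 3 × 2 × 2 = 12 moderator-by-outcome tests without correction. It is too strong to say that the gate protects nothing. But labelling and intervals serve that purpose in an exploratory study without suppressing the result.
- **Openness.** The condition is pre-stated, and the objectives section can be read as naming the aim while the analysis section gives the operating rule. That removes any suggestion of concealment but does not make the rule suit the hypothesis.

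**Conclusion.** The point holds, chiefly for the moderator hypothesis. The protocol announces the analysis without a condition, then makes it depend on two significant average effects and offers no substitute if they are absent. A significant average effect is not a precondition for moderation, and benefit confined to a subgroup makes it less likely. The hypothesis says only that some participants benefit more, so the dilution is strongest when the others benefit little or not at all.

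The size depends on the information retained, the true average effect, the assumed bias test, and whether one gambling outcome is enough. The claim that the analysis would mostly not run is justified only under heavy information loss or a diluted average effect. A clearly larger true effect would open the gate far more often: at f = 0.25, about 99% of the time at 91 per module and 57% to 75% at 36. No primary estimate or error rate is affected.

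**What to change.** Delete the condition from the Data analysis section. State that the prespecified moderation and moderated mediation models will be fitted for both modules whatever the ANOVA results, that interactions and indirect effects will be reported with bootstrap confidence intervals, and that all of them are exploratory.

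The cost is one changed sentence and a few extra models on data the protocol already collects. The downside is that, at the lower end of the retained sample, the estimates will be imprecise and without multiplicity control; the report should say so.
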